### Study procedures

#### Baseline data collection and randomisation to electronic medication taking measurement

Eligible patients registered with the practice are identified by the practice nurse. Baseline data from the notes is recorded by the practice nurse and anonymised to provide data from which to characterise the population from which participants were recruited. Eligible patients are sent a letter from the practice including study details, a questionnaire asking about basic demographics, medication regimen, self-reported medication adherence, and beliefs about taking diabetes medicines without missing a day (Table 1 and Table 2). If willing to help further, a phone call is made by the practice nurse to the patient to arrange a study appointment.

**Table 1 T1:** Trial measures and timing

	Baseline visit	Before 8 week visit	At 8 week visit	After 8 week visit	Final visit at 20-weeks
Basic demographics	x				

Medication	x		x		x
Co-morbidity	x				
**Clinical measures**					
Weight	x				x
Blood pressure	x				x
HbA1c (Central laboratory)	x		x		x
**Adherence**					
Electronic medication monitor for preceding period			x (50%)		x
Self-report (MARS) Diabetes		x			x
Drug concentrations			x		x
**Psychological**					
TPB† Direct measures and intention	x	x		x	
TPB† Indirect measures	x	x		x	
Time and location of taking medicines					x
Communication with practice nurse					x
**Quality of Life**					
Short-Form 12‡	x				x
Diabetes Treatment Satisfaction Questionnaire					x
Hypoglycaemia			x		x

^‡^ 12-Item short form Medical Outcomes Study health survey questionnaire.

^†^ Theory of Planned Behaviour.

**Table 2 T2:** Theory of Planned Behaviour measures of belief and intention towards taking oral glucose-lowering medications

**Variable name**	**Number of items†**	**Sample question**
Direct attitude	2	It is beneficial for me to take my diabetes medicines without missing a day
Direct subjective norm (injunctive)	2	Most people who are important to me think I should take my diabetes medicines without missing a day
Direct subjective norm (descriptive)	1	If they were taking part in this study, most people who are important to me would take their diabetes medicines without missing a day
Direct perceived behavioural control	3	It is difficult for me to take my diabetes medicines without missing a day
Indirect attitude	7	If I were to take my diabetes medicines without missing a day, it would keep my diabetes under control
Indirect subjective norm (injunctive)	3	Members of my family or close relatives would approve of me taking my diabetes medicines without missing a day
Indirect perceived behavioural control	4	Changes to my daily routine would make it more difficult for me to take my diabetes medicines without missing a day
Intention	2	I intend to take my diabetes medicines without missing a day

†Each measured on a 7-point scale from 1 = strongly disagree to 7 = strongly agree

Willing patients attend a baseline recruitment consultation of 40 minutes with their practice nurse. In advance of the visit patients are allocated to be dispensed medication in the electronic medication-monitoring device or in standard packaging. Informed consent is obtained and additional clinical data collected. Blood tests are taken, and questionnaires completed. For those allocated to the electronic medication-monitoring device, its use is explained, and the practice dispenser or pharmacist dispenses the patient's usual prescription for metformin or alternative oral glucose lowering agent in the device. For those allocated to standard packaging, the practice dispenser or pharmacist dispenses medication in standard blister-packs. A follow-up visit is arranged in eight weeks and, in advance of the visit, the patient is randomised to be allocated to receive the intervention or control visit.

#### Intervention and control visit

Prior to the eight-week study visit patients are sent a questionnaire to be completed at home and returned to the coordinating centre in a sealed envelope by post. At the eight-week visit, patients allocated to the intervention take part in a 50 minutes interview with the practice nurse including the intervention and data collection. The control visit lasts approximately 20 minutes in which the data are collected. All patients at the eight week visit have blood samples taken and inquiry made about any possible adverse events including hypoglycaemia. A postal questionnaire is completed one week after the eight week visit.

#### Follow up to 20 weeks

Final follow up for all patients at 20 weeks involves a visit to the practice nurse and includes a blood sample for measurement of HbA1c and drug concentrations, and a final questionnaire.

### Measurement

#### Primary outcome for intervention trial

The primary outcome for the intervention is the percentage of days on which the prescribed dose of main hypoglycaemic medication is taken as prescribed, measured with the TrackCap electronic medication monitor over a 12-week period from eight to twenty weeks.

#### Primary outcome for measurement-effect trial

The primary behavioural outcome for the measurement effect of the use of an electronic medication-monitoring device compared with standard packaging is change in self reported adherence measured with the Medication Adherence Report Schedule (MARS). The primary clinical outcome for the measurement effect is mean HbA1c at eight weeks.

#### Secondary outcomes for intervention trial

Secondary outcomes are HbA1c, well-being measured with the 12-item Short Form Medical Outcomes Study health survey questionnaire (Short Form-12) [22] and treatment satisfaction measured with the Diabetes Treatment Satisfaction Questionnaire (DTSQ) [23].

#### Additional measures of medication adherence

Other measures include serum drug concentrations and self-reported measures of medication adherence (MARS) [24], and dispensing records to complement electronic medication-monitoring. Drug concentrations will be collected to explore whether the electronic medication-monitoring device records of timing of doses relate to the presence of therapeutic concentrations at study visits.

#### Psychological and process measures

A questionnaire based on the Theory of Planned Behaviour is used to assess attitude, subjective norm, perceived behavioural control, and intention to take diabetes medicines without missing a day. The questionnaire also assesses perceived consequences of taking diabetes medication (behavioural beliefs); perceived views of significant others about taking diabetes medication (normative beliefs); perceived factors that make taking diabetes medication easier or difficult (control beliefs). These measures are based on our earlier pilot work [19].

We are using a measure to assess patients' ratings of communication with nurses (covering the ability to tell the nurse personal or troubling things and feeling understood) [25], and ask open-ended questions about when and where medications are usually taken. Tape recordings of consultations are used to assess fidelity of intervention delivery, using a-priori criteria. The intervention facilitators record adherence to techniques specified in the intervention script on standardised forms.

#### Baseline measures to characterise participants

Socio-demographic and clinical measures include measures of duration of diabetes, overall drug regimen and numbers of prescribed medication doses. For the purposes of characterising the eligible population and randomisation at baseline, the last practice-recorded HbA1c is also recorded.

### Sample size

The trial is planned to follow-up 200 patients, providing 80% power at the 5% significance level to detect a difference in means between randomised groups of 5% (1.5 days per month difference) in the percentage of days on which the correct number of doses is taken. This was based on an estimate of the standard deviation of this measure of 13.5% in a pilot study for the trial conducted in 2001 in Newmarket, Cambridgeshire (personal communication [name]). Assuming a follow-up rate of 85%, a maximum of 250 participants would need to be recruited.

For the measurement effect we can detect a difference of one point in the MARS self-reported adherence measure (a small to moderate effect size) [24], with 80% power and a two sided test at the 5% level with a conservative estimate of a 2.5% standard deviation. We will also detect a 0.5% difference in HbA1c at eight weeks with 80% power at the 5% level assuming a standard deviation of 1.25% for HbA1c.

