**Methods and Design:**

The SAMS (Supported Adherence to Medication Study) trial is a primary care based multi-centre randomised controlled trial among 200 patients with type 2 diabetes and an HbA1c of 7.5% or above. It is designed to evaluate the efficacy of a two-component motivational intervention based on the Theory of Planned Behaviour and volitional action planning to support medication adherence compared with standard care. The intervention is delivered by practice nurses. Nurses were trained using a workshop approach with role play and supervised using assessment of tape-recorded consultations. The trial has a two parallel groups design with an unbalanced three-to-two individual randomisation eight weeks after recruitment with twelve week follow-up. The primary outcome is medication adherence measured using an electronic medication monitor over 12 weeks and expressed as the difference between intervention and control in mean percentage of days on which the correct number of medication doses is taken. Subgroup analyses will explore impact of number of medications taken, age, HbA1c, and self-reported adherence at baseline on outcomes. The study also measures the effect of dispensing medication to trial participants packaged in the electronic medication-monitoring device compared with conventional medication packaging. This will be achieved through one-to-one randomisation at recruitment to these conditions with assessment of the difference between groups in self-report of medication adherence and change in mean HbA1c from baseline to eight weeks. Anonymised demographic data are collected on non-respondents. Central randomisation is carried out independently of trial co-ordination and practices using minimisation to adjust for selected confounders.

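### The stated inputs give about 72–73% power for the primary outcome, not the stated 80%, and recruiting the maximum of 250 does not close the gap

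*Protocol article*

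**What the plan says.** The Sample size section sets the target: "The trial is planned to follow-up 200 patients". It describes that number as "providing 80% power at the 5% significance level to detect a difference in means between randomised groups of 5% (1.5 days per month difference"). The variability assumption is "an estimate of the standard deviation of this measure of 13.5% in a pilot study". The recruitment sentence follows: "Assuming a follow-up rate of 85%, a maximum of 250 participants would need to be recruited".

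The allocation ratio is given in the Abstract (Methods and Design), which describes an "unbalanced three-to-two individual randomisation eight weeks after recruitment". The Trial design section confirms that the main randomisation is unbalanced.

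The primary power sentence does not say whether the test is one- or two-sided. The Intervention effect part of the Analysis section plans a difference in means with a 95% confidence interval, which corresponds to a two-sided 5% test. The second paragraph of the Sample size section, on the measurement effect, specifies a two-sided test at the 5% level.

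**The concern.** The section prints every input to a standard two-group calculation together with the result, and the result does not follow from the inputs. This is not detail that an article may leave to a fuller document.

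The sentence is the only justification given for the size of the primary comparison. As written, it credits the trial with a 20% risk of missing the target difference, when the risk on its own figures is more than a quarter. The Discussion makes a follow-on trial conditional on evidence of efficacy and says that even very small effects matter. A reader weighing an inconclusive result should therefore have the right figure for what the trial could detect.

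**Working it through.** **Inputs**
- Patients followed up: 200 (Sample size)
- Allocation 3:2, hence 120 and 80 (Abstract; Trial design)
- Target difference: 5 percentage points (Sample size)
- Standard deviation: 13.5 percentage points (Sample size), taken as equal in both arms
- Two-sided 5% level: z = 1.960 (from the 95% confidence interval in Analysis, Intervention effect)
- 80% power: z = 0.842, so the sum of the two is 2.802

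**1. Attempt to reproduce the stated 80%**

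SE = 13.5 × √(1/120 + 1/80) = 1.949

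5 / 1.949 = 2.566

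Power = Φ(2.566 − 1.960) = Φ(0.606) = 72.8%. The noncentral t gives 72.4%. The stated figure is not reproduced.

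**2. Is the 3:2 ratio the cause?**

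With 100 and 100, SE = 13.5 × √(2/100) = 1.909 and 5 / 1.909 = 2.619. Power = Φ(0.659) = 74.5% (t: 74.1%). The unequal allocation costs less than 2 percentage points, and most of the shortfall remains without it.

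**3. Number needed for 80%**

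At 3:2: N = 2.802² × 13.5² × (1/0.6 + 1/0.4) / 5² = 238.4, or 240 in whole 3:2 groups (144 and 96).

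At 1:1: N = 2.802² × 13.5² × 4 / 5² = 228.9, or 230.

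**4. What 200 can detect**

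Detectable difference at 80% power, 120 against 80: 2.802 × 1.949 = 5.46 points, which is 0.0546 × 30 = 1.6 days in a 30-day month.

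Standard deviation at which 200 would suffice: 5 / (2.802 × √(1/120 + 1/80)) = 12.4 (12.6 at 1:1). Rounding does not turn 13.5 into either value.

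**5. Does the recruitment figure help?**

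- To follow up 200 at 85%: 200 / 0.85 = 235.3, so 236 recruits.
- From 250 recruits at 85%: 250 × 0.85 = 212.5 followed up. At 3:2, SE = 13.5 × √(1/127.5 + 1/85) = 1.890 and 5 / 1.890 = 2.645. Power = Φ(0.685) = 75.3% (t: 75.0%).
- To follow up 240 at 85%: 240 / 0.85 = 282.4, so 283 recruits.

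**6. Internal comparison**

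Both measurement-effect calculations in the same section have a standard deviation 2.5 times the difference (2.5 against 1 point of MARS; 1.25 against 0.5 of HbA1c). With balanced groups, N = 4 × 2.802² × 2.5² = 196.2, or 198 in whole equal groups. These two claims hold with 200 under the same two-sided formula. The fault is confined to the primary outcome.

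**The case against.** The strongest defence is that the primary power sentence does not state sidedness. A one-sided 5% test at 3:2 gives Φ(2.566 − 1.645) = 82%, so that may be where the figure came from. It does not rescue the statement, because the primary result is to be reported with a 95% confidence interval and the companion calculation in the same section is explicitly two-sided.

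Another possible origin is reading 1.5 days against a 28-day month, which is 5.36 points. That gives 80.1% at 1:1, but 78.5% at the trial's 3:2 ratio, and it replaces the stated 5%.

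Multiple imputation might be said to bring all 250 recruits into the analysis, but it does not create the outcome information that was lost. Even 250 with no loss at all would give only 81.8%, and that contradicts the assumed 85% follow-up.

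Some stronger readings are tempting but are not supported:
- *The recruitment figure is a second error.* A reader might infer this because 200 / 0.85 is 236, not 250. The article calls 250 a maximum, and 236 lies below it, so the two are compatible. What stands is that 250 does not restore 80% power, and that is the same shortfall.
- *The Abstract contradicts the Sample size section.* The Abstract speaks of a "multi-centre randomised controlled trial among 200 patients with type 2 diabetes", and a reader might infer that 200 is the number randomised, with lower power still after losses. The Sample size section makes clear that 200 is the follow-up target, so the Abstract is a condensation.
- *Baseline adjustment would recover the shortfall.* This would need a baseline–outcome correlation of about 0.40. The article gives no such correlation and builds no variance reduction into the calculation. Table 1 shows monitor data before the main randomisation for only 50% of patients.

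The defence is also right about the scale of the harm. The estimate, its confidence interval and the type I error are unaffected, and the interval will show the precision actually achieved.

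**Conclusion.** The primary power statement is wrong as written. On the article's own inputs, 200 patients followed up at 3:2 give about 72–73% two-sided power for a 5-point difference, so the type II error is about 27–28% instead of 20%. Power of 80% needs about 240 followed up, 20% more than planned, or a target difference of about 5.5 points. At the recruitment ceiling of 250 with 85% follow-up, power is about 75%.

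This rests on a two-sided 5% test, a common standard deviation of 13.5, independent patients and no gain from covariate adjustment. The bootstrap interval is taken to perform like the usual large-sample comparison of means. Only the sidedness assumption would change the conclusion if reversed, and the article's own text points to two-sided.

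It does not follow that the trial is invalid or that its other sample-size claims fail. Both measurement-effect calculations reproduce.

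**What to change.** Replace the primary power sentence with wording such as:

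> With 200 patients followed up (120:80), a standard deviation of 13.5% and a two-sided 5% test, the trial has about 72% power for a 5% difference, or 80% power for a difference of about 5.5%.

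Extend the recruitment sentence to say that at 85% follow-up 236 recruits are needed to follow up 200, and that the ceiling of 250 would give about 212 followed up and about 75% power.

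This changes only wording; the price is a less favourable stated power. Keeping the 80% claim for 5 points would instead require about 240 followed up and about 283 recruited, which is above the stated maximum.

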### Analysis

#### Intervention effect

Analysis will be by intention-to-treat using multiple imputation for those with missing data by the method of Rubin [26]. This will be supported by a sensitivity analysis reporting all cases where the primary outcome is available and using optimistic and pessimistic scenarios with the imputed estimates for missing data [27]. The mean percentage of days on which the correct number of doses is taken will be compared between the groups allocated to intervention and control, using a non-parametric bootstrap method to derive the difference in means with a 95% confidence interval [28,29].

#### Measurement effect

The primary behavioural outcome for the assessment of measurement effect is self-reported adherence (MARS) at eight weeks compared between groups allocated to use of the medication monitor compared to those allocated to dispensing of medicines in standard packaging. The primary clinical outcome is HbA1c at 8-weeks compared between groups. In order to increase the precision of estimated intervention effects continuous measures will be analysed with adjustment for the baseline covariate prior to the first randomisation, if available, with missing baseline data included by the missing indicator method [27].

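### The adjustment rule dates baseline before the first randomisation, so the 8-to-20-week intervention comparison has no covariate rule tied to its own randomisation; the cost is precision, not bias

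*Protocol article*

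**What the plan says.** The trial has two sequential randomisations (Trial design). The first, at recruitment, allocates an electronic monitor or standard packaging, with follow-up at week 8. The second, at week 8, allocates intervention or control, with follow-up at week 20.

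The only adjustment rule is in the Analysis section under Measurement effect. Its aim is introduced as "In order to increase the precision of estimated intervention effects". It then says that "continuous measures will be analysed with adjustment for the baseline covariate prior to the first randomisation, if available". Patients who lack such a value stay in the analysis through a missing indicator.

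The Intervention effect paragraph specifies multiple imputation and compares the groups "using a non-parametric bootstrap method to derive the difference in means with a 95% confidence interval". It names no covariate. The primary outcome is "measured with the TrackCap electronic medication monitor over a 12-week period from eight to twenty weeks". For the intervention trial, "Secondary outcomes are HbA1c, well-being measured with" the SF-12, with treatment satisfaction also listed.

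Table 1 shows what exists by week 8. The row "Electronic medication monitor for preceding period" is marked at the 8-week visit for 50% of patients. The row "HbA1c (Central laboratory") is marked at baseline, week 8 and week 20. The section on the intervention and control visit confirms that blood is taken from all patients at week 8.

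**The concern.** The stated aim of the rule and the date of its covariate belong to different comparisons. A value taken before the first randomisation is the right baseline for packaging. For a treatment allocated eight weeks later it is eight weeks old. For the primary outcome it has no like-for-like form, because nobody is monitored before the first randomisation.

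The two possible readings both leave a gap. If the rule covers the intervention comparison, it points to week-0 values. If it covers only the measurement effect, as its heading suggests, no adjustment is named for the intervention comparison. On neither reading does the document adjust that comparison for the week-8 HbA1c, planned for everyone, or the 0-to-8-week monitor record, planned for half. At stake is the precision of the primary estimate and of the secondary HbA1c estimate.

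**Working it through.** **Inputs from the protocol.** Sample size section: 200 followed up, difference 5 percentage points, SD 13.5, 5% significance level, HbA1c SD 1.25 (given for the week-8 comparison). Abstract: 3:2 allocation, hence 120 versus 80. Table 1: run-in monitor record in 50%.

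**Assumptions.** All correlations are assumed, since none is given. The test is taken as two-sided, since sidedness is not stated for this outcome. The HbA1c SD of 1.25 is taken to hold at week 20. Monitor records are split 60/60 in the intervention arm and 40/40 in the control arm, which is reasonable because the second minimisation includes the first allocation.

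**Step 1: the plan's own figure.** Unadjusted SE = 13.5 × √(1/120 + 1/80) = 13.5 × 0.1443 = 1.949. Power = Φ(5/1.949 − 1.96) = Φ(0.606) = 72.8%. The stated 80% is not reproduced (one-sided, the same inputs give 82.1%). That is a separate sample-size matter; here 72.8% serves only as the starting point.

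**Step 2: primary outcome, covariate in half the patients.** With correlation ρ, residual variance is σ²(1 − ρ²) where the record exists and σ² where it does not. With an indicator for absence, the pooled variance is σ²(1 − ρ²/2), so SE = 1.949 × √(1 − ρ²/2).

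| ρ | Variance cut, ρ²/2 | SE | Power |
|---|---|---|---|
| 0.4 | 8% | 1.869 | 76% |
| 0.5 | 12.5% | 1.823 | 78% |
| 0.6 | 18% | 1.765 | 81% |
| 0.7 | 24.5% | 1.693 | 84% |

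A simulation of this model (4,000 runs per correlation) gave 78.5% power at ρ = 0.5 and 84.0% at ρ = 0.7, against 73–74% unadjusted. Power reaches 80% only if ρ is about 0.57 or more. A record in all patients would have given 84% at ρ = 0.5, so the half coverage limits the gain.

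**Step 3: HbA1c at week 20.** Half-width = 1.96 × 1.25 × √(1/120 + 1/80) × √(1 − r²) = 0.354 × √(1 − r²).

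- Week-0 covariate, r = 0.5 to 0.6: 0.354 × 0.866 = 0.31, down to 0.354 × 0.8 = 0.28.
- Week-8 covariate, r = 0.7 to 0.8: 0.354 × 0.714 = 0.25, down to 0.354 × 0.6 = 0.21.

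**Step 4: is adjustment for week-8 values legitimate?** The second allocation is made ahead of the 8-week visit, so the blood sample and the monitor reading come after allocation. The sample is drawn at the visit where the intervention is given, so it cannot yet reflect that session. The monitor record covers the eight weeks before it. Absence of a record by design follows the first allocation, which the second minimisation balances.

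**The case against.** The strongest reply is that the sentence sits under Measurement effect, directly after the two week-8 outcomes, where its baseline is correct. On that reading the rule takes nothing from the intervention comparison. An unadjusted bootstrap difference in means is valid, and a condensed article may leave covariates to an analysis plan that is not shown. This stands in part: the heading favours the narrow reading. It does not remove the point, because the sentence gives its aim as intervention effects, and its reach therefore has to be settled.

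A reader might infer that the plan throws away its strongest predictors. The documents do not support this. They give no correlations, and the imputation model is not described, so the week-8 values may be used there. A reader might also infer bias. Adjusting for a week-0 value, or not adjusting, leaves the randomised comparison unbiased.

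Two further objections stand as limits. Some device-arm patients may lack a usable record or a week-8 sample, and that loss arises after allocation, so first-stage allocation alone is not a complete missing indicator. Also, week-0 HbA1c is in the second minimisation, so it should stay in the model beside the week-8 value.

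**Conclusion.** The point holds as a matter of scope and efficiency. The only adjustment rule is aimed at intervention effects but dated for the measurement comparison, and the protocol fixes no baseline relative to the 8-week randomisation. Validity is not affected.

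The size rests on assumed correlations. On the primary outcome the gain is about 3 power points at 0.4 and about 11 at 0.7, with complete follow-up of 200, equal SDs and a two-sided test. The HbA1c gain depends wholly on how much better week 8 predicts week 20 than week 0 does. The change should be made because the values are already scheduled, but it should not be presented as a repair of the sample-size calculation.

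**What to change.** 1. Limit the existing rule explicitly to the measurement effect.
2. For intervention outcomes, define baseline relative to the 8-week randomisation.
3. For 20-week HbA1c, adjust for the 8-week value and keep the week-0 value, which is in the minimisation.
4. For the primary outcome, report a bootstrap difference in means adjusted for the percentage of correct days in weeks 0 to 8 in those who have it. Put first-stage allocation in the model, with a missing indicator that also covers device-arm patients without a usable record.

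The cost is a wording change, to be settled before outcomes are seen by arm. It needs no new data, visits or patients, and the missing-indicator method is already in the plan.
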